### Interventions

All recruited patients will receive combined spinal and epidural anesthesia at the L3-4 level. For all the patients, cefamandole (2 g) will be administered intravenously 30 minutes before and after surgery. Low-molecular-weight heparin (4,500 U) for thromboprophylaxis will be administered subcutaneously 8 hours postoperatively and then once daily until week 2. In group E, the heparin administration will be delayed until epidural catheter withdrawal on postoperative day (POD) 2. A standardized intraoperative regimen for fluid administration will be applied which consists of 0.9% saline at 5 ml/kg per hour and colloid (Voluven; Fresenius Kabi, Bad Homburg, Germany) at 7.5 ml/kg per hour.

For multi-model pain management, preoperative oral doses of 400 mg celecoxib daily will be administered from day 2 before surgery. Postoperatively, all patients will receive 40 mg of parecoxib sodium twice daily intravenously until POD 3, followed by oral doses of 200 mg celecoxib every 12 hours until discharge. Tramadol hydrochloride injection will be applied for rescue analgesia.

The same surgeon will perform all operations. A Gemini MK II prosthesis (LINK, Hamburg, Germany) will be inserted via a standard medial parapatellar approach in all patients.

#### **
*Cocktail anesthetic preparation*
**

Cocktail anesthetic will be prepared for continuous intra-articular infusion, containing 150 mg ropivacaine (20 ml), 3 mg morphine sulfate (0.3 ml), 30 mg ketorolac tromethamine (1 ml), 0.5 μg 1:1000 epinephrine (0.5 ml), mixed with normal saline into a total volume of 150 ml.

#### **
*Continuous intra-articular infusion anesthesia group (group C)*
**

In group C, 50 ml of cocktail anesthetic will be applied via periarticular infiltration before insertion of the prosthesis. A multi-holed catheter will be placed into the lateral parapatellar gutter. The remaining 100 ml will be used as continuous intra-articular infusion with a patient-controlled analgesic (PCA) pump (Fornia, Zhuhai, China) at a speed of 2 ml/hour. After the wound is sutured, the catheter will be connected to the PCA pump which is activated after surgery and removed 48 hours later. The PCA pump will be set to deliver a 0.5-ml dose with a 15-minute lockout interval.

#### **
*Epidural infusion anesthesia group (group E)*
**

In group E, the epidural catheter position will be checked with a test dose of 3 ml lidocaine-adrenalin (20 mg/ml and 5 μg/ml), followed by a bolus of 7 ml ropivacaine (2 mg/ml). A PCA pump containing 200 mg of ropivacaine (2 mg/ml) and 4 mg of morphine (0.04 mg/ml) will be connected with a flow rate of 2 ml/hour for 48 hours postoperatively. The PCA will be programmed to provide a 0.5-ml dose with a lockout interval of 15 minutes.

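### The group C cocktail lists epinephrine as 0.5 μg and also as 0.5 ml of 1:1000, which is 500 μg: a 1000-fold contradiction in a study-drug recipe

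*Protocol article*

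**What the plan says.** The Interventions section of the Protocol article, under Cocktail anesthetic preparation, specifies a single mixture for the intra-articular arm. Three ingredients are each given as a mass with a volume: "containing 150 mg ropivacaine (20 ml), 3 mg morphine sulfate (0.3 ml), 30 mg ketorolac tromethamine (1 ml". The fourth is given as a mass, a ratio strength and a volume together: "0.5 μg 1:1000 epinephrine (0.5 ml), mixed with normal saline into a total volume of 150 ml".

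The whole mixture goes to group C, in two parts. For the first, "50 ml of cocktail anesthetic will be applied via periarticular infiltration before insertion of the prosthesis". For the second, "The remaining 100 ml will be used as continuous intra-articular infusion", delivered by pump over 48 hours. The Sample size section plans 107 patients for this group. The epinephrine content of the cocktail is stated nowhere else in the article.

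**The concern.** Mass, strength and volume are not independent: any two of them fix the third. The epinephrine line gives all three, and they disagree.

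The line is a preparation instruction for the experimental treatment. Someone who works from the mass makes a mixture with almost no epinephrine. Someone who works from the strength and volume makes one with 1000 times as much. Epinephrine is vasoactive and the trial enrols patients aged 50 to 80, so the instruction should not leave the preparer to decide which figure to ignore. It also bears on what the trial tests: a reader who wants to repeat or interpret the comparison cannot tell from the article how much epinephrine group C received.

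**Working it through.** **Inputs** (all from Interventions, Cocktail anesthetic preparation and the group C paragraph)
- Epinephrine mass: 0.5 μg
- Epinephrine strength: 1:1000, by definition 1 g per 1000 ml = 1 mg/ml = 1000 μg/ml
- Epinephrine volume: 0.5 ml
- Final volume of the mixture: 150 ml, of which 50 ml is infiltrated and 100 ml is loaded for infusion

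**Does the stated mass follow from the other two figures?**
mass = strength × volume = 1000 μg/ml × 0.5 ml = 500 μg = 0.5 mg.
The stated mass is 0.5 μg, and 500 / 0.5 = 1000. The stated figure is not reproduced.

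**Does holding a different pair fixed rescue the line?**
- Mass and volume kept: 0.5 μg / 0.5 ml = 1 μg/ml, which is 1:1,000,000 and not 1:1000.
- Mass and strength kept: 0.5 μg / (1000 μg/ml) = 0.0005 ml, not 0.5 ml.

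No reading makes the three figures agree.

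**Is the whole recipe unreliable, or only this line?**
- Ropivacaine: 150 mg / 20 ml = 7.5 mg/ml
- Morphine: 3 mg / 0.3 ml = 10 mg/ml
- Ketorolac: 30 mg / 1 ml = 30 mg/ml

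These lines give no separate strength to check against, but the stock concentrations they imply are plausible. The group E pump can be checked fully and agrees with itself: 200 mg / (2 mg/ml) = 100 ml for ropivacaine, and 4 mg / (0.04 mg/ml) = 100 ml for morphine. The fault is confined to epinephrine.

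**What each reading would deliver**

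| Quantity | If 0.5 μg | If 0.5 ml of 1:1000 |
|---|---|---|
| Epinephrine in 150 ml | 0.5 μg | 500 μg |
| Concentration (÷ 150) | 0.0033 μg/ml (1:300,000,000) | 3.33 μg/ml (1:300,000) |
| In 50 ml infiltration | 0.17 μg | 167 μg |
| In 100 ml infusion, if fully delivered | 0.33 μg | 333 μg |

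**The case against.** The strongest reply is that the recipe can still be followed. Each ingredient has a volume to draw up. For epinephrine, strength and volume alone define the step: take 0.5 ml of 1:1000 and make up to 150 ml. The other reading would mean drawing 0.0005 ml, which no preparer is likely to do unnoticed. Changing the mass unit from μg to mg makes all three figures agree, so this is probably a slip in one unit. It may not be in the operational preparation sheet at all, because the article condenses a fuller protocol. The article also gives no dose limit by which to call either amount unsafe.

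Most of this is fair. That 0.5 mg was intended is the more plausible inference, and nothing here shows that 500 μg is harmful or that the preparation sheet carries the error. What does not follow is that the line may stand. The article does not resolve the conflict, and a dosing instruction should not depend on the preparer guessing which number to disregard. The allowance for condensed articles covers what is left out, not a figure that is printed and wrong.

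A fault in reading the PDF text (mg read as μg) cannot be excluded entirely, but nothing points to one. The same unit appears correctly for the group E test dose (5 μg/ml), and the mg units of the neighbouring ingredients are intact.

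**Conclusion.** The concern holds. The epinephrine line contradicts itself by a factor of exactly 1000: 0.5 μg as a mass, against 500 μg from the stated strength and volume. The only convention used is the definition of 1:1000 as 1 g in 1000 ml; everything else is printed in the article.

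The consequence is limited in kind but serious in place. Sample size, endpoints and analysis are untouched. What is affected is the definition of the experimental treatment for every group C patient, and the safety of preparing it. Strength and volume together point to 0.5 mg, but that is an inference, and this review does not decide which figure is right. Because the error is certain, concerns a dose and costs little to remove, it must be fixed.

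**What to change.** Reconcile the mass, strength and volume of the epinephrine line with the pharmacy preparation sheet. Correct whichever figure is wrong, so that all three agree, in the protocol and in every document derived from it, before the first patient is dosed. Adding the final concentration in the 150 ml mixture would give the preparer an independent check; it would read 3.33 μg/ml if 0.5 mg is confirmed.

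The cost is one corrected line, one pharmacy check and a notification to the ethics committee. Nothing in the design, sample size or analysis has to change.

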### Sample size

Calculation of sample size was based on two previous studies [20,25]. We assumed that postoperative pain during the 24- to 48-hour period will reach peak value and need effective pain control. Mean VAS scores over 24 to 48 hours for the two modes of analgesia were extracted. Group sample sizes of 93 for each group will achieve 80% power to detect a difference of 1.0 between the null hypothesis that both group means are 2.8 and the alternative hypothesis that the mean of group E is 1.8, with estimated group standard deviations of 3.1 and 1.4 and with a significance level (alpha) of 0.05 using a two-sided *t*-test. We plan to enroll a total of 214 participants with 107 in each group, allowing for a 15% withdrawal rate.

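### In both arms the 100 ml pump can supply 48 hours of background infusion plus only 8 patient boluses, although the lockout allows 192

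*Protocol article*

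**What the plan says.** All settings are in the Interventions section of the protocol article.

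- **Group C, volume.** The cocktail is "mixed with normal saline into a total volume of 150 ml". Of this, "50 ml of cocktail anesthetic will be applied via periarticular infiltration before insertion of the prosthesis". Then: "The remaining 100 ml will be used as continuous intra-articular infusion with a patient-controlled analgesic (PCA) pump", at 2 ml/hour.
- **Group C, duration and bolus.** The pump is one "which is activated after surgery and removed 48 hours later". On demand doses: "The PCA pump will be set to deliver a 0.5-ml dose with a 15-minute lockout interval".
- **Group E.** The text gives "A PCA pump containing 200 mg of ropivacaine (2 mg/ml") together with 4 mg of morphine at 0.04 mg/ml, and this pump "will be connected with a flow rate of 2 ml/hour for 48 hours postoperatively". Bolus size and lockout are the same as in group C.

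The article states no refill, second reservoir or cap on the number of boluses for either arm.

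The Sample size section ties the trial to the second postoperative day: "Mean VAS scores over 24 to 48 hours for the two modes of analgesia were extracted". The Primary outcome measures section schedules visual analogue scale (VAS) readings at 26, 34 and 42 hours within that window, and makes tramadol frequency and consumption over the first 3 postoperative days a primary measure as well.

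**The concern.** The article fixes five quantities for each pump: volume, background rate, bolus size, lockout and duration. The first two and the last almost exhaust one another before any bolus is given, yet a bolus function is programmed. A site that follows the text cannot be sure of delivering 48 hours of infusion to a patient who uses that function.

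The stake for the analysis is what the comparison means. Emptying is triggered by demand. If patients with more pain press more often, they are the ones whose assigned infusion stops early. Tramadol use, and at higher demand the later VAS readings, would then partly reflect an exhausted reservoir and not the analgesic technique. Any such emptying would fall between 25 and 48 hours, which lies within the period the sample size is built on.

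**Working it through.** **Inputs** (Interventions section): 150 ml cocktail and 50 ml infiltration in group C; 200 mg ropivacaine at 2 mg/ml and 4 mg morphine at 0.04 mg/ml in group E; in both arms 2 ml/hour, 0.5 ml bolus, 15-minute lockout, 48 hours. Reading times are from Primary outcome measures.

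**1. Reservoir volume.**
- Group C: 150 − 50 = 100 ml, which reproduces the stated figure.
- Group E: 200 / 2 = 100 ml, and 4 / 0.04 = 100 ml.

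**2. Volume left for boluses.**
- Background use: 2 × 48 = 96 ml.
- Remainder: 100 − 96 = 4 ml, and 4 / 0.5 = 8 boluses, or one per 6 hours on average.

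**3. What the lockout permits.**
- 60 / 15 = 4 boluses per hour, and 4 × 48 = 192 boluses.
- 192 × 0.5 = 96 ml, so the highest possible draw is 96 + 96 = 192 ml against 100 ml held.

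**4. Time to empty.** With an average of *b* boluses per hour, T = 100 / (2 + 0.5*b*).

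| Boluses per hour | Pump empty at |
|---|---|
| 1 per 6 h | 48.0 h |
| 1 per 4 h | 47.1 h |
| 1 per 2 h | 44.4 h |
| 1 | 40.0 h |
| 2 | 33.3 h |
| 3 | 28.6 h |
| 4 (lockout maximum) | 25.0 h |

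Each bolus beyond the eighth shortens the infusion by 0.5 / 2 = 0.25 hours, or 15 minutes. Emptying at 25 hours takes 4 × 25 = 100 boluses, one at every opportunity.

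**5. When a scheduled reading is affected.** To empty the pump by hour *t*, a patient must have taken (100 − 2*t*) / 0.5 boluses.

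| VAS reading | Volume to be used as boluses | Boluses needed | Average per hour | Lockout maximum by then |
|---|---|---|---|---|
| 26 h | 100 − 52 = 48 ml | 96 | 3.69 | 104 |
| 34 h | 100 − 68 = 32 ml | 64 | 1.88 | 136 |
| 42 h | 100 − 84 = 16 ml | 32 | 0.76 | 168 |

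So 8 boluses is the threshold for losing some infusion time, and about 32 by 42 hours is the threshold for affecting any scheduled VAS reading in the sizing window. At one bolus every 2 hours the pump empties at 44.4 hours, after the last of these readings.

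**The case against.** The strongest reply is that this is a thin margin and not a contradiction. The 100 ml does cover the background infusion for 48 hours. A lockout limits how often a dose can be given and does not promise 192 of them, and a finite reservoir can itself serve as a total limit. That is a fair reading of the lockout. It does not settle the matter, because the article gives 48 hours as the duration and does not present the reservoir as a limit. Once a patient takes a ninth bolus, the stated duration cannot be met from the stated volume.

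Other parts of the reply stand and limit the point:

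- **Hour 25.** A reader might infer that pumps will be running dry from hour 25, at the start of the sizing window. That needs uninterrupted maximum demand day and night, and the article gives no demand figure.
- **VAS in the window.** A reader might also infer that every patient above 8 boluses contributes a compromised reading. The second table above shows otherwise.
- **Bias.** Volume, rate, bolus, lockout and duration are identical in the two arms, so nothing here favours one arm by construction. If one arm empties sooner because its patients hurt more, that is arguably a consequence of the regimen as assigned, which a comparison of regimens captures. Demand could still differ: the sample size assumes a lower mean VAS in group E (1.8 against 2.8), and a bolus carries ropivacaine at 1 mg/ml in group C (150 mg in 150 ml) against 2 mg/ml in group E. Neither fact gives the size or the direction of any difference in emptying.
- **Readings without a pump.** VAS at 50, 58, 64 and 72 hours falls after the pump period in both arms, so readings without infusion are already part of the design.
- **Recording.** The article does not list pump data among its outcomes. It is a condensed report, and the full protocol may cover this, so the silence is not a fault in itself.

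**Conclusion.** The point holds as a moderate one. In both arms the stated volume, rate, bolus setting and duration fit together only for patients who take at most 8 boluses in 48 hours, against 192 that the lockout allows, and the article states no refill or cap. Beyond 8 boluses the infusion ends early, by 15 minutes for each further bolus.

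The calculation assumes that boluses are drawn from the same 100 ml in addition to the background flow, that all 100 ml is usable, that group E's 7 ml starting bolus is given separately from the pump, and that pump time and VAS time both run from the end of surgery.

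The documents do not support the stronger conclusion that the 24 to 48 hour VAS comparison is compromised or biased. That would require demand of roughly 0.76 boluses per hour or more sustained to 42 hours, in enough patients to matter, and for bias it would also require demand that differs by arm. With no demand figure given, the size of the effect is unknown and could be negligible.

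**What to change.** Reconcile the statements on pump volume, background rate, bolus setting and duration in the group C and group E paragraphs of the Interventions section, so that they can all be met together. This review does not say which of them should change.

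Where the pump allows it, record for each patient the boluses or total volume delivered and the time of emptying. Report these by arm beside tramadol frequency and consumption, so that a reader can see how often the infusion ended early and whether that differed between arms.

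The cost is a correction to the intervention text and a small amount of extra data capture. No patients, visits or procedures are added.

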### Randomization and blinding

Random assignment was performed before surgery by using a computer generated, blocked random-allocation sequence with a 1:1 ratio. This study cannot be blinded because the different catheter placement is obvious.

### Primary outcome measures

#### **
*Visual analogue scale*
**

The visual analog scale (VAS) has been used extensively for rating pain intensity in previous studies [22-24]. Postoperative pain at 2, 6, 10, 18, 26, 34, 42, 50, 58, 64, and 72 hours after surgery will be recorded using a VAS. The VAS consists of a 10-cm horizontal line with 1-cm vertical lines at each end labeled "no pain" (left side) and "worst possible pain" (right side).

#### **
*Rescue analgesia frequency and consumption*
**

Usually the need for supplementary treatment with systemic opioids is a reliable indicator when concerned about postoperative pain control. In previous studies, it has been argued that the use of strong or long-term rescue analgesia in both treatment groups may have reduced pain too much and “washed out” any differences between the two treatments. In this study, we use tramadol hydrochloride injection, which is a mid-intensity analgesic that will facilitate observing the differences in pain control between groups. The frequency and total consumption during the first 3 postoperative days will be recorded.

#### **
*Active range of motion*
**

Traditionally, range of motion has been used as an outcome measure after TKA to evaluate functional recovery and the success of the type of analgesia used [4-6,12]. However, we think active range of motion (A-ROM) represents a more realistic criterion for assessment of functioning and analgesia efficiency after TKA. A-ROM will be measured in the first 3 postoperative days and at the 3-month and 6-month follow-up.

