### Recruitment and consent

Patients scheduled for primary TKA at the Department of Orthopedic Surgery, Guang Dong Provincial Hospital of TCM, will be recruited, with a target sample size of 214 subjects. All candidates will go through a standardized interview process and receive more information about the study and the treatments. The participants’ written consents will be obtained. The purpose and procedures, and potential risks and benefits, of the study will also be explained thoroughly to the participants. Participants are able to withdraw from the study at any time without consequence. The trial will be executed from February 2014 to December 2015 including enrollment and follow-up (Figure 1).

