### Data analysis

The statistical analysis will be performed using SPSS (Version 17.0) software (SPSS Inc., Shanghai, China). Normally distributed continuous variables will be compared using Student’s *t*-test. VAS and A-ROM will be analyzed with repeated measures for general linear models and multivariate analysis of variance. Data will be expressed as means (standard deviation), absolute numbers, and frequencies, when appropriate. *P* < 0.05 will be considered statistically significant for all comparisons.

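### The VAS schedule has no preoperative reading and the VAS analysis no baseline term, so a modest and nearly costless gain in precision is forgone

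*Protocol article*

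**What the plan says.** Under Primary outcome measures, the VAS schedule is set out hour by hour: "Postoperative pain at 2, 6, 10, 18, 26, 34, 42, 50, 58, 64, and 72 hours after surgery will be recorded using a VAS". The earliest reading is 2 hours after the operation.

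Under Data analysis, the method is: "VAS and A-ROM will be analyzed with repeated measures for general linear models and multivariate analysis of variance". No baseline or other covariate is named, and none is ruled out.

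Under Sample size, the trial is sized on VAS alone: "Mean VAS scores over 24 to 48 hours for the two modes of analgesia were extracted". The calculation is an unadjusted t-test: "Group sample sizes of 93 for each group will achieve 80% power to detect a difference of 1.0", with "estimated group standard deviations of 3.1 and 1.4".

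Under Recruitment and consent, there is already a contact with every candidate: "All candidates will go through a standardized interview process". Its content is not described.

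**The concern.** Patients coming to knee replacement for osteoarthritis differ in how much pain they already have and in how they use a pain scale. If part of that difference carries over into the pain scores after surgery, it stays in the error term of an unadjusted comparison. A preoperative score used as a covariate removes that part at the same sample size.

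The choice of covariates can be left to an analysis plan. The reading itself cannot: a VAS mark not taken before surgery cannot be recovered later. That is why the assessment schedule is the main point and the model statement comes second.

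At stake is some power on the only outcome with a stated power, and the ability to show and adjust for a chance difference between the groups in preoperative pain. The validity of the comparison is not at stake.

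**Working it through.** **Inputs.** From Sample size: difference 1.0 (the alternative is stated against the null that "both group means are 2.8 and the alternative hypothesis that the mean of group E is 1.8"), SDs 3.1 and 1.4, 93 per group, and "significance level (alpha) of 0.05 using a two-sided" t-test. The correlation r is not in the document; values from 0.1 to 0.5 are assumed.

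**Step 1: reproduce the stated power.**
- Variances: 3.1² = 9.61 and 1.4² = 1.96; sum 11.57.
- Standard error of the difference at 93 per group: √(11.57 / 93) = 0.353.
- Noncentrality: 1.0 / 0.353 = 2.835.
- Unequal-variance (Welch) degrees of freedom: 92 × 11.57² / (9.61² + 1.96²) = 128, critical t = 1.979.
- Power from the noncentral t: **0.803**. The smallest n reaching 0.80 this way is 93 per group. The plan's figure reproduces, and it assumes no baseline adjustment.

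**Step 2: add a baseline covariate with equal r in both arms.** Each arm's variance is multiplied by (1 − r²), and Step 1 is repeated. For r = 0.3, for example, the sum is 11.57 × 0.91 = 10.53.

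**Step 3: add a baseline covariate with one common slope.** Equal r in arms with SDs 3.1 and 1.4 needs a slope 3.1 / 1.4 = 2.2 times steeper in one arm, since randomised arms share the same expected preoperative spread. A single covariate with one slope instead removes the same absolute variance from each arm. With r defined in the SD-1.4 arm, that amount is r² × 1.96. For r = 0.3 it is 0.176 per arm, so the sum becomes 11.57 − 0.353 = 11.22, a 3.0% reduction. In the other arm r is then 0.3 × 1.4 / 3.1 = 0.14.

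**Power at 93 per group:**

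| Assumed r | Equal r in both arms | Common slope, r in the SD-1.4 arm |
|---|---|---|
| 0 | 0.803 | 0.803 |
| 0.1 | 0.807 | 0.805 |
| 0.2 | 0.819 | 0.809 |
| 0.3 | 0.839 | 0.815 |
| 0.5 | 0.901 | 0.836 |

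**In patients.** With equal r, the number per group for 80% power falls from 93 to 92, 89, 85 and 70 for r = 0.1, 0.2, 0.3 and 0.5.

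**The case against.** The strongest reply is that nothing here is wrong. Randomisation keeps the unadjusted comparison unbiased, the stated 93 per group reaches its target without a covariate, and chance imbalance is already allowed for in the test's type I error. All of that stands.

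Second, this is a condensed article. Covariates are usually named in an analysis plan, which is not shown, and a general linear model can take one. The article gives no other baseline measurements either, so a preoperative VAS might be taken and simply not reported. This stands in part. It weakens the point about the model, but the VAS schedule is precise to the hour and contains no preoperative time.

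Third, chronic osteoarthritis pain and acute pain during a 48-hour infusion with rescue analgesia may correlate only weakly. This stands too, and at r = 0.1 the gain is trivial.

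A reader might also infer stronger versions that the document does not support:
- **That the SD of 3.1 shows large preoperative spread.** Randomised arms have the same expected preoperative spread, so baseline pain alone cannot explain 3.1 against 1.4.
- **That the lack of blinding makes the covariate more necessary.** A baseline covariate does nothing about unblinded reporting.
- **That the covariate is needed because about 91 per group remain after a 15% loss from 107.** That shortfall comes from how the withdrawal allowance was applied and is a separate matter.

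**Conclusion.** The point holds as a missed efficiency. The stated VAS schedule and analysis leave out a baseline that could only raise precision or leave it about the same. At 93 per group the gain over 0.803 runs from almost nothing (r = 0.1) to 0.839 at r = 0.3 with equal correlations, but only to 0.815 under a common slope. The 0.901 at r = 0.5 needs both a high correlation and a much steeper slope in one arm, and nothing in the document supports either. A gain of a few percentage points at most is the more likely result.

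This rests on assumed values of r and on the plan's own SDs and difference. It also takes the published schedule to be the full list of VAS readings. It should be rated an optional, cheap improvement.

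**What to change.** - In Primary outcome measures, add one resting VAS mark before surgery to the schedule, for example at the existing standardized interview. If the full protocol already collects it, state so.
- In Data analysis, name it as a prespecified covariate in the VAS model and in the contrast of 24 to 48 hour means.
- Keep patients with a missing preoperative mark by imputing the mean of the covariate.

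The cost is one more form entry and one more model term, with no extra patients or procedures. The downside is an additional item to collect, for little or no return if the correlation proves to be near zero.
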